### Cell transplantation

Cell delivery is predicted to be performed about 6 hours after bone marrow cell harvesting. Arterial accesses will be performed using femoral or radial approach. All patients will receive 10,000 IU of heparin IV after sheet insertion. When non-infarct related vessel intervention is planned, it will be performed before cell transfer. Electrocardiography, pulse oximetry, and vitalsigns will be monitored throughout the procedure, as well as symptoms.

A 6-F guiding catheter will be placed at the ostium of the infarct-related coronary artery. After positioning the catheter inside the coronary ostium, a dosage of isossorbide mononitrate will be administered (total of 1 ml = 10 mg). Then, a coronary will be performed in a calibrated system in order to visualize the coronary blood flow before injection. At least one projection for evaluating "TIMI frame count" will be performed with a 30 frame/sec filming, attempting to visualize the distal coronary bed.

After TIMI 3 flow scrutiny, an over-the-wire (OTW) balloon catheter (Maverick^® ^Over-The-Wire balloon, Boston Scientific, Natick, MA, USA) will be positioned inside the previously implanted stent in the culprit vessel to transiently interrupt anterograde blood flow during infusions through a stop-flow technique. The use of the *over-the-wire *balloon with over 0.5 mm of the reference lumen diameter in a low pressure (< 4ATM) is recommended. The ideal balloon extent is 9 mm, limited to the edge of the previously implanted stent.

Cells solution will be infused through the central lumen of the balloon catheter, in about 40 seconds, during 3 coronary occlusions, each lasting 2 – 3 minutes, followed by 2 minutes of balloon deflation.

A final coronary angiography will be performed at the end of all procedures as control in order to ascertain TIMI frame count pre and post PCI and cell transfer.

#### ✓ Baseline exams (before bone marrow aspiration) and follow up

The chronogram of the study is shown in table 2. Briefly, patients will be submitted to a clinical evaluation at hospital admission and clinical data regarding blood pressure, heart rate and Killip and Kimball classification will be stored. Patients will be standardly treated with chemical or mechanical reperfusion according to the local center availability. A coronary angiography and an invasive ventriculography will be performed in all patients before angioplasty in order to evaluate inclusion/exclusion criteria. Patients submitted to fibrinolysis must have the angioplasty of the infarct-related coronary artery performed up to 48 hours after reperfusion. Laboratorial dosage will be also performed as shown in table 2.

**Table 2 T2:** Chronogram of the study

Informed Consent	□											
Randomization				□								

**Exams/Visits**					**After Injection**							
										
	Baseline	pos-reperfusion	3^rd^–5^th ^day of reperfusion	5^th ^to 7^th ^day	Up to 1 h	12 h	24 h	6^th ^to 9^th ^day	1 month	3 months	6 months	1 year

Medical visit	□		□						□	□	□	□
ALT, AST, AP, PT, aPTT and INR			□									
Total Cholesterol, LDL-cholesterol, HDL-cholesterol and Triglycerides	□											
Full blood panel, Glucose, Urea, Creatinine, Na+, K+, CRP			□				□		□		□	
CK-MB mass, Troponin I	□		□	□		□	□					
Electrocardiogram	□	□	□		□	□	□		□	□	□	□
Echocardiogram			□						□	□	□	□
Cardiac MRI								□			□	
Coronary angiography	□										□	
Cells transplant				□								
Cells sample storage				□								
SF-36, Minnesota and Seattle QOL			□						□		□	□
QALY Evaluation									□		□	□

ALT and AST: alanine and aspartate aminotransferases, respectively; AP: alkaline phosphatase; INR: international normatized ratio; PT: prothrombin time; aPTT: activated partial thromboplastin time; CRP: C-reactive protein; MRI: magnetic resonance image; QOL: quality of life questionnaires; QALY: quality adjusted life year.

Three to five days after reperfusion therapy (mechanical or chemical), patients will be submitted to another clinical evaluation, including an EKG, an echocardiogram and laboratory tests, from which results will be used as baseline data for the research protocol, before injection procedure. A new CK-MB mass and troponin dosage will be performed in the morning preceding the injection procedure and timely in the 24 hours following the injection.

The baseline cardiac magnetic resonance imaging (MRI) will be performed between day 6 and 9 after the AMI-related coronary artery recanalization. This exam may be performed either in the hospital or at a reference hospital. All imaging exams will be evaluated off line by the core lab specified in the appendix [see Addition file 1].

Hospital discharge is predicted 24 hours after cell transplantation unless otherwise indicated, making a total length of stay of approximately 7 days. Patients will be provided with clopidogrel, aspirin and pravastatin during the entire study and treated at the discretion of the attending physician.

Patients will be followed for 1 year after the procedure according to the chronogram of the study shown in table 2. All imaging exams will be stored and sent to the core lab for independent analysis as specified in the appendix [see Addition file 1].

Cardiac MRI will be done by the local centers with commercially available software, electrocardiographic triggering, and cardiac-phased array coil. LV function will be assessed by the use of steady-state free-precession gradient-echo sequence (SSFP). Eight to twelve short axis slices will be acquired during a 10–15 seconds breath-holding allowing for coverage of the entire LV. Additionally, 3 long-axis views will also be acquired: 2-chamber and 4-chamber views and left ventricle out flow tract. Regional LV function will be assessed by measuring systolic wall thickening in the infarct region, the adjacent border zone and remote myocardium and semi-quantitatively assessed, using a 17-segment model[14].

Transmural extent of late hyper-enhancement within each segment will be graded according to the following classification: 0–25%, 26–50%, 51–75%, and more than 75% hyper-enhancement. Segmental functional recovery is defined as an increase from hypokinetic to normokinetic, from akinetic to hypokinetic or normokinetic, or from dyskinetic to akinetic, hypokinetic, or normokinetic. Infarct size will be measured by planimetry.

Microvascular obstruction will be defined on late enhanced images taken early (within 2–5 min) after injection of 0.20 mmol/kg of gadopentetate dimeglumine (Gd-DTPA), in the LV short and long axis at the same locations used for cine-MRI–as a dark, subendocardial zone within the infarct area.

For assessment of global and regional LV function and calculation of LV mass, endocardial and epicardial borders will be traced in end-diastolic and end-systolic short-axis slices. LV end-diastolic and end-systolic volumes (LVEDV and LVESV) will be calculated and indexed to body-surface area. All MRI studies will be independently analyzed on an off-line workstation, core laboratory as defined in the appendix [see Additional file 1].

### Sample size

Sample size calculation was performed according to the following assumptions:

▪ Based on Pró-Cardíaco Hospital and InCor's coronary care databank, after selecting AMI patients Killip I; II or III, we have concluded that the left ventricle EF presented a Gaussian distribution with an average of 37.35% and standard deviation of 7.9%).

▪ An expert panel has evaluated that an improvement of +5% (relative gain of +15.9%) on the EF would represent a significant clinical improvement for the patient.

Considering as clinically beneficial a 5% increase in EF% with a standard deviation of 5%, 143 patients per arm are needed to detect a significant difference between groups with 95% confidence and 80% power. Considering a 5% loss during follow up, we estimated 150 patients per arm.

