### Hypothesis

The main hypothesis of this trial is that patients submitted to autologous bone marrow stem cell transplantation will present, on average, at least 5% higher EF in comparison with the placebo group after 6 months follow up.

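### The 143 patients per arm do not follow from the printed difference and standard deviation in the planned two-group test, and the protocol does not show which number is wrong

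*Protocol article*

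**What the plan says.** The Sample size section of the protocol article gives three sets of figures.

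- A hospital databank of infarction patients, with EF described as Gaussian with "an average of 37.35% and standard deviation of 7.9"%.
- A clinical threshold set by experts: "an improvement of +5% (relative gain of +15.9%) on the EF".
- The calculation: "Considering as clinically beneficial a 5% increase in EF% with a standard deviation of 5%, 143 patients per arm are needed to detect" a group difference "with 95% confidence and 80% power", raised to 150 per arm for 5% loss to follow-up.

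The Hypothesis section makes the 5% a between-group contrast: "at least 5% higher EF in comparison with the placebo group after 6 months follow up". The section on end points and statistical analysis defines the primary endpoint as EF change from baseline to 6 months. It compares the groups by Student's t test or Mann-Whitney, with one interim analysis on patients 1 to 150 (reject if p ≤ 0.0050) and a final analysis on all 300 (reject if p ≤ 0.04806). Sidedness is not stated.

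**The concern.** A difference equal to one standard deviation is a very large standardised effect, and a two-group comparison of that size needs fewer than 20 patients per arm. A figure of 143 signals a standardised effect of about one third. The difference, SD, confidence, power and result are all printed, so condensation into an article does not explain the mismatch: the numbers contradict each other on the page.

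This calculation is the only justification given for randomising 300 patients to marrow aspiration and intracoronary infusion. If it cannot be reproduced, a reader does not know what difference the trial was built to detect. Nor can those planning the interim analysis judge how likely the boundary is to be crossed under the design assumptions.

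**Working it through.** **Inputs.** Difference Δ = 5 points and SD = 5 (Sample size); alternative SD = 7.9 and mean 37.35 (databank, same section); α = 0.05, taken as two-sided; power 80%; 1:1 allocation; two-group t test (End points and statistical analysis).

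**Formula.** Normal approximation, per arm: n = 2 × (1.960 + 0.842)² × (SD/Δ)² = 15.70 × (SD/Δ)². The exact t test adds about one patient per arm.

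**Attempt to reproduce 143.** A relative 5% is 0.05 × 37.35 = 1.87 points.

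| Δ (points) | SD | 15.70 × (SD/Δ)² | t test, per arm |
|---|---|---|---|
| 5 | 5 | 15.7 | 17 |
| 5 | 7.9 | 39.2 | 41 |
| 1.87 (5% relative) | 5 | 112.5 | 114 |
| 1.87 (5% relative) | 7.9 | 280.9 | 282 |

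For Δ = 5 and SD = 5, the exact t-test power is 78.1% at 16 per arm and 80.7% at 17. The stated 143 is 143/17 = 8.4 times the figure for the printed inputs, and 143/41 = 3.5 times the figure with the databank SD.

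**Other variants.**
- One-sided testing needs fewer: 14 per arm for 5 and 5.
- A Mann-Whitney efficiency of 0.864 gives 19 for 5 and 5.
- Multiplying the SD by √2, as for an uncorrelated change score, gives 33 (SD 5) or 80 (SD 7.9).
- A 15.9% relative gain (0.159 × 37.35 = 5.94 points) gives 13 (SD 5) or 29 (SD 7.9).

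None of these gives 143.

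**What would give 143.**
- *Two-sample, back-solved.* The standardised difference with 80% power at 143 per arm is 0.3324. For 5 points that means SD = 5/0.3324 = 15.04. With SD exactly 15, 15.70 × 9 = 141.3 and the t test gives 143, with 80.2% power. SD 15 is an assumption; it is stated nowhere.
- *One-sample.* The one-sample or paired formula drops the factor of 2: 7.85 × (7.9/1.87)² is about 140.5, and the t test gives 142.4, so 143. This uses only printed figures but is the wrong formula for two independent arms. In a two-arm comparison, 143 per arm would have about 51% power for that difference.

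**Dropout step.** 143/0.95 = 150.5, against 150 stated. This is consistent, so the mismatch lies before it.

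**Consequences, by SD.** The 80%-power detectable difference is 0.3324 × SD. For the interim, 75 per arm is assumed (half of 150), the true difference is 5, and the exact t test is taken at p ≤ 0.0050.

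| SD | Power at 143 per arm for 5 points | Detectable difference (80%) | Chance of crossing at interim |
|---|---|---|---|
| 5 | over 99.9% | 1.66 | about 99.9% |
| 7.9 | over 99.9% | 2.63 | about 85% |
| 15 (assumed) | 80% | about 5 | about 21% |

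**Relative gain.** 5/37.35 = 13.4%, not 15.9%. A gain of 15.9% on 37.35 is 5.94 points; 5 points being 15.9% implies a mean of 5/0.159 = 31.4.

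**The case against.** The best defence is that the document does not show which figure is wrong. A two-sample t test with 5 points and SD 15 gives exactly 143, so a lost digit in the printed SD is plausible. In that case the stated power is correct and only the SD is misprinted. This stands. A reader might infer from the mismatch that the 80% power claim is false and that the trial is greatly oversized. The documents support that only if SD 5 or 7.9 is the true SD of the analysed quantity.

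Three further limits also stand. First, it is tempting to say that no reading whatever yields 143, but the one-sample calculation does, from printed figures alone; the claim holds for two-sample readings. Second, a reader might conclude that the trial would almost certainly stop at the interim. That fits SD 5, but the chance is about 85% at SD 7.9 and about 21% at SD 15. Third, 7.9 is the spread of EF in a databank, whereas the primary endpoint is EF change, so 7.9 need not apply to it.

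The relative-gain discrepancy does not enter the calculation of 143 and adds no weight to it.

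The defence does not remove the central fact. SD 15 appears nowhere and is nearly twice the databank SD, and the sentence as printed is arithmetically wrong for the planned test.

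**Conclusion.** The concern holds in this form: the sample size does not follow from its printed inputs in the planned two-group t test. The stated 143 per arm compares with 17 for the inputs in the same sentence, 41 with the databank SD, and 114 or 282 if the 5% is relative. This rests on a two-sided 5% test, 80% power and equal allocation; one-sided testing widens the gap for the printed inputs.

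The source of the error cannot be settled from the article. The power, detectable difference and interim crossing probability are therefore conditional on the SD, and none of them should be quoted as a property of the design until the SD is known. In particular, the documents do not establish that the trial is overpowered. They also do not establish that it is underpowered for 5 points: on the printed SDs it has ample power.

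The 15.9% against 13.4% is a separate, lesser inconsistency, and here too the article does not show whether the percentage or the baseline is at fault.

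**What to change.** Rewrite the Sample size paragraph so that it can be reproduced:

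- use one scale, absolute EF points;
- give one SD, for the EF change that is analysed, with its source;
- state the sidedness and the two-sample formula;
- report what 143 per arm then provides, as power for 5 points or as the difference detectable with 80% power. If the SD is 5 or 7.9, that difference is 1.66 or 2.63 points, and the case for 300 patients should rest on it. If an SD near 15 was used, say so and justify it against the databank's 7.9.

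Separately, reconcile the relative gain with 5 points on 37.35 by correcting either the percentage or the baseline it was taken from.

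The cost is one reissued paragraph. The 300 patients, the procedures and the analysis schedule need not change.

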### End points and statiscal analysis

The primary endpoint of this trial is the global left ventricular EF change from baseline to 6 month follow-up.

The following secondary endpoints will be evaluated for up to 1 year of follow up: major cardiovascular events (all-cause mortality, acute myocardial infarction, stroke and hospital admission due to cardiovascular cause); reintervention of the AMI-related artery and of non-related arteries; by MRI regional wall motion, wall thickening, and volume of late contrast enhancement; quality of life assessment using the Short-Form 36, Minnesota Living with Heart Failure and Seattle Angina questionnaires; cost-effectiveness and cost-utility evaluation of ABMMC implant versus conventional treatment.

All outcomes will be analyzed by intention to treat.

Primary outcome will be analyzed by comparing EF, measured by MRI, between groups, using student t test or Mann-Whitney according to the sample distribution. Two evaluations are programmed:

1. Interim analysis, which will use data related to patients 1 to 150;

2. Final analysis, which will use data related to all 300 patients.

Secondary outcomes will only be evaluated after the main final analyses. Mortality and functional class improvement will be analyzed by non-corrected chi-square test. Continuous variables with normal distribution will be analyzed by t student test and ANOVA for repeated measures. Continuous variables with asymmetric distribution and quality of life scores will be analyzed by Mann-Whitney test and ANOVA for repeated measures.

The frequency of serious adverse events (which brings eminent risk of death or permanent disability) will be analyzed by chi-square or Fisher's test.

The trial can be interrupted after interim analysis; using the O'Brien and Fleming rule for two sequential tests and the 5%, in which the null hypothesis is rejected if:

• p ≤ 0,0050 in the first analysis;

• p ≤ 0.04806 in the final analysis.

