## Abstract

**Background:**

Myocardial infarction remains as a major cause of mortality worldwide and a high rate of survivors develop heart failure as a sequel, resulting in a high morbidity and elevated expenditures for health system resources. We have designed a multicenter trial to test for the efficacy of autologous bone marrow (ABM) mononuclear cell (MC) transplantation in this subgroup of patients. The main hypothesis to be tested is that treated patients will have a significantly higher ejection fraction (EF) improvement after 6 months than controls.

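### The primary endpoint is EF change, but the stated analysis compares EF with an unadjusted test: name one primary variable and adjust for a named pre-injection EF

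*Protocol article*

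**What the plan says.** The section on end points and statistical analysis defines the outcome as a change: "The primary endpoint of this trial is the global left ventricular EF change from baseline to 6 month follow-up". Shortly afterwards it gives the analysis: "Primary outcome will be analyzed by comparing EF, measured by MRI, between groups, using student t test or Mann-Whitney according to the sample distribution". That sentence mentions neither change nor a baseline term.

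The hypotheses divide in the same way. The abstract expects that "treated patients will have a significantly higher ejection fraction (EF) improvement after 6 months than controls", which is a statement about change. The Hypothesis section expects "at least 5% higher EF in comparison with the placebo group after 6 months follow up", which is a statement about level.

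The Sample size section gives two SDs. One describes EF in a hospital databank: "left ventricle EF presented a Gaussian distribution with an average of 37.35% and standard deviation of 7.9" (percent). The other enters the calculation: "Considering as clinically beneficial a 5% increase in EF% with a standard deviation of 5" (percent). The text does not say whether this second SD belongs to EF or to its change.

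On baseline measurements:
- The eligibility criteria require EF of 50% or less.
- The section on baseline exams takes its pre-injection research baseline from the day 3 to 5 assessment, which includes an echocardiogram.
- The MRI called baseline is done on days 6 to 9 after recanalization, and Table 2 marks it under the columns after injection.
- Marrow is harvested on days 5 to 7, and cells are delivered about 6 hours later.

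**The concern.** EF at 6 months and change in EF are different outcome variables. They have different variances and can give different p-values from the same data. A confirmatory trial needs one of them fixed in advance, all the more so here because the same test drives a stopping decision at 150 patients. If the choice stayed open until the data were seen, the two tests would give two chances of a significant result.

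Both versions also ignore information already in hand. A pre-injection EF is scheduled for every patient, and to the extent that it predicts 6-month EF, leaving it out of the model wastes precision.

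**Working it through.** **1. Can the sample size show which variable was meant?** The stated result is "143 patients per arm are needed to detect a significant difference between groups with 95% confidence and 80% power". Two-sided alpha of 0.05 is assumed. The normal formula is n per arm = 2 × (1.960 + 0.842)² × (SD/difference)², that is 15.70 × (SD/difference)².
- Difference 5, SD 5: 15.70, so 16 per arm (17 by exact t).
- Difference 5, SD 7.9: 39.2, so 40 per arm (41 by exact t).
- Difference 5, SD 15: 141.3, so 142 per arm (143 by exact t).

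The plan's 143 does not follow from its own inputs; an SD of about 15 would be needed. That is a separate problem. Here it means only that the sample size cannot tell us whether level or change was planned.

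**2. Relative precision.** Let rho be the correlation between baseline EF and 6-month EF. The documents do not give it, so it is an assumption, shown as a range. With equal SDs at both times, variance relative to the unadjusted comparison of 6-month EF is:
- change score: 2(1 − rho)
- ANCOVA: 1 − rho²
- ANCOVA relative to change: (1 − rho²)/[2(1 − rho)] = (1 + rho)/2

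| rho | change / level | ANCOVA / level | ANCOVA / change |
|---|---|---|---|
| 0.3 | 1.40 | 0.91 | 0.65 |
| 0.5 | 1.00 | 0.75 | 0.75 |
| 0.7 | 0.60 | 0.51 | 0.85 |
| 0.8 | 0.40 | 0.36 | 0.90 |

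The ranking of level and change reverses at rho = 0.5. ANCOVA is no worse than either in large samples. The last column applies only when the covariate is the same measurement that the change score subtracts.

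**3. Where 0.80 comes from.** If the SD of 5 is the SD of change and 7.9 is the SD of EF at both times, rho = 1 − 25/(2 × 7.9²) = 0.80. The ANCOVA residual SD is then 7.9 × √(1 − 0.64) = 4.74. Both readings are assumptions.

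**4. Two candidate tests.** Under no effect and equal SDs, the level and change statistics correlate at √((1 − rho)/2): 0.59, 0.50 and 0.32 at rho 0.3, 0.5 and 0.8. The chance that at least one reaches p < 0.05 is then 8.8%, 9.1% and 9.5%. This applies only if the choice really is left until after the data are seen.

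**5. A baseline measured after injection.** Suppose the true effect is 5 points, rho is 0.5, and the day 6 to 9 MRI already carries 20% of the effect (an illustrative assumption). The change score then targets 5 − 0.2 × 5 = 4.0, and ANCOVA on that MRI targets 5 − 0.5 × 0.2 × 5 = 4.5. With a true pre-injection covariate, ANCOVA targets 5.0.

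**The case against.** The strongest reply is that the analysis sentence is shorthand. Its subject is the primary outcome, already defined as change, and it may only be adding the modality and the test. It never says EF at 6 months. That reading is possible. But the Hypothesis section independently describes a level, and the sample size does not settle the matter, so one explicit sentence is still needed.

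A second reply is that a t test on change is valid and that covariate adjustment is often left to an analysis plan not shown here. It is valid, and the absence of a covariate would not be a finding on its own. The article, however, itself names the test and describes two different variables. Nor do the documents show that the analyst is in fact free to choose after seeing the data, since an unseen plan may fix the variable. The 9% figures describe what is at risk if it does not.

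Three stronger readings are tempting and unsupported:
- **Testing the level has 2.5 times the variance of testing change.** This is 7.9²/5² = 62.4/25, which is the rho = 0.80 scenario alone. It rests on an unlabelled SD that does not reproduce 143. At rho 0.3 it is change that has 40% more variance.
- **Chance imbalance in baseline EF biases the unadjusted result.** Under randomization it is sampling error, which the t test already covers.
- **The trial is underpowered for the level.** With SD 7.9, a difference of 5 and 143 per arm, the standardized effect is 5/(7.9 × √(2/143)) = 5.35, and power exceeds 99.9%. On the plan's own SDs the loss is of precision, with no threat to power.

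**Conclusion.** The point holds as an ambiguity in the primary variable together with an avoidable loss of precision. Given a true pre-injection baseline, both contrasts are unbiased for the same mean difference. Adjustment removes 9% to 64% of the variance of the level comparison as rho runs from 0.3 to 0.8. With equal SDs and a same-measure baseline, it removes 35% down to 10% of the variance of the change comparison. No single figure in that range can be claimed from the documents.

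A reader might infer that ANCOVA alone settles the conflict, or that modelling change is equivalent to modelling 6-month EF. The equivalence holds only when the covariate is the same measurement that was subtracted. Here the pre-injection EF assigned to the research baseline is by echocardiogram and the outcome is by MRI, so the covariate has to be named.

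**What to change.** State one primary analysis: 6-month MRI EF in a linear model with treatment and a named EF measured before injection as covariate. Report the adjusted mean difference in EF points with its confidence interval.
- **Covariate:** the day 3 to 5 echocardiogram EF already scheduled, or MRI EF only if it is obtained before injection.
- **Avoid:** using an MRI taken after injection as covariate or as the subtracted baseline, and subtracting echocardiogram EF from MRI EF.
- **Both looks:** use the same model at the interim and final analyses, with the unadjusted comparison as a sensitivity analysis.
- **Wording:** align the abstract, the Hypothesis section and the end points section, and reconcile the timing of the baseline MRI with that of harvest and injection in the text and Table 2.

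With the echocardiogram covariate the cost is a few sentences and no new data. Guaranteeing a pre-injection MRI would require a change to the imaging schedule. The downside is small: if echocardiogram EF correlates weakly with 6-month MRI EF, the gain is modest, about 9% less variance than the level comparison at rho 0.3.

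### The primary test is chosen from the observed outcome distribution, so the primary result may rest on a rank test that does not address the stated hypothesis of a difference in mean EF

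*Protocol article*

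**What the plan says.** All of this is in the protocol article.

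- **Hypothesis section.** Patients given cells "will present, on average, at least 5% higher EF in comparison with the placebo group after 6 months follow up". This is a statement about means.
- **Sample size section.** The calculation uses a difference and a standard deviation: "Considering as clinically beneficial a 5% increase in EF% with a standard deviation of 5%, 143 patients per arm are needed". It also describes databank EF as Gaussian, with mean 37.35% and SD 7.9%.
- **End points and statistical analysis section, endpoint.** "The primary endpoint of this trial is the global left ventricular EF change from baseline to 6 month follow-up".
- **Same section, analysis.** "Primary outcome will be analyzed by comparing EF, measured by MRI, between groups", "using student t test or Mann-Whitney according to the sample distribution".
- **Same section, looks.** There is an interim analysis on the first 150 patients and a final analysis on all 300, "using the O'Brien and Fleming rule for two sequential tests", with limits p ≤ 0.0050 and p ≤ 0.04806.

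Nothing in the article fixes one of the two tests as primary, requires the same test at both looks, or names the effect measure to be reported if Mann-Whitney is used.

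**The concern.** The t test and Mann-Whitney answer different questions. The t test compares means, which is the quantity in the hypothesis. Mann-Whitney asks whether a randomly chosen treated patient tends to have a higher value than a randomly chosen control. The two agree when one arm is a shifted copy of the other. They can part when the treatment changes the shape of the distribution.

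Under the rule as written, the outcome data decide which question the trial answers. Two consequences follow if shapes differ between arms. Mann-Whitney can reject when mean EF change is equal, and it can miss a real mean gain that is concentrated in a minority of patients. In either case the headline p-value would not come with an estimate in EF points to set against the 5-point target.

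**Working it through.** **1. The plan's own boundaries.** For one pre-fixed statistic and an interim look at half the information (correlation √0.5 between looks), two-sided limits of 0.0050 and 0.04806 give an overall alpha of 0.04998. The boundaries are sound for a single test.

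**2. Same distribution in both arms.** Assumptions: 75 then 150 per arm; Mann-Whitney chosen at a look if Shapiro-Wilk gives p < 0.05 in either arm; 8,000 simulated trials per shape (Monte Carlo standard error about 0.24 points). Overall type I error across both looks:

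| Shape | t test always | Mann-Whitney always | Switching rule |
|---|---|---|---|
| Normal | 5.3% | 5.0% | 5.4% |
| Lognormal | 4.9% | 4.5% | 4.5% |
| Gamma (shape 4) | 4.9% | 4.7% | 4.7% |
| t, 4 df | 5.0% | 4.8% | 4.8% |
| Exponential | 5.4% | 5.0% | 5.0% |

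The two looks used different tests in 12.9% of trials for normal data and 14.7% for t with 4 df, without material inflation.

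**3. Equal means, different shapes.** Assumptions: final look only, 143 per arm, 5% level, Shapiro-Wilk at 5% on pooled centred residuals, control normal with mean 0 and SD 5. Ranges cover repeated runs of 4,000 to 6,000 trials.

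- *Treated arm right-skewed* (gamma with shape 4, rescaled to mean 0 and SD 5; skewness 2/√4 = 1). The t test rejects 4.8–5.8%, Mann-Whitney 9.5–10.4%, the rule 8.7–9.4%. Nearly all the rank-test rejections favour placebo, because at equal means the skewed arm has the lower median. The rule favours cells in only about 0.6% of trials.
- *Treated arm left-skewed* (mirror image). The direction reverses: the rule favours cells in about 8.5% of trials, against a nominal 2.5% in that direction.
- *20% gain 8 points and 80% lose 2, plus normal noise with SD 4* (mean 0.2×8 − 0.8×2 = 0). The t test rejects about 5%, Mann-Whitney about 9%, the rule 7–8%. The rule favours cells in about 1.4% of trials.

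**4. A minority with a strong benefit.** 15% of treated patients gain 12 points, the rest gain nothing, and SD is otherwise 5.

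- Mean difference: 0.15 × 12 = 1.8.
- t test: treated variance 25 + 144 × 0.15 × 0.85 = 43.36; SE = √[(43.36 + 25)/143] = 0.691; z = 1.8/0.691 = 2.60; power ≈ Φ(2.60 − 1.96) ≈ 74%.
- Mann-Whitney: P(treated > control) = 0.15 × Φ(12/(5√2)) + 0.85 × 0.5 = 0.15 × 0.955 + 0.425 = 0.568; null SE = √[287/(12 × 143²)] = 0.0342; z = 0.068/0.0342 ≈ 2.0; power ≈ 52%.
- Simulation gives 74% for the t test, 52% for Mann-Whitney and 57–58% for the switching rule.

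**A milder pattern.** With 20% gaining 8 points and the rest unchanged, the rule chose Mann-Whitney in only about 15% of trials. Power was 66.9%, against 68.9% for the t test.

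The figure of 143 per arm is used here only as the planned number. Whether it follows from the stated difference and SD is a separate matter.

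**The case against.** **The criterion may sit in an unseen document.** A journal article condenses the full protocol, so a missing normality test or threshold is no fault. That is right, and the point does not rest on it. The article itself states that the distribution decides the test, and a precise criterion elsewhere would still let the data move the primary analysis away from the mean.

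**Error control.** A reader might infer that choosing the test from the data inflates type I error in general, or invalidates the O'Brien-Fleming limits. The two-look results do not support this: with one common distribution the rule stays at 4.5–5.4%. Taking the smaller of the two p-values would give 6.3–7.7%, but the article does not allow that; it says the distribution decides.

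**False claims of benefit.** A reader might also take the 9% as a raised chance of wrongly declaring that cells work. With right skew the opposite holds, since false claims of benefit fall below the nominal 2.5%. They rise only with left skew. Nor does benefit confined to a minority produce equal means by itself. The balanced scenario needs the other 80% to lose 2 points each, and nothing in the article suggests that. Where a minority benefits and nobody loses, the mean difference is real and the cost is lost power, not false rejection.

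**Practical effect.** If EF change is close to normal, the rule will usually select the t test and little changes. That is fair, but the Gaussian statement in the sample size section concerns databank EF, not six-month change.

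**Conclusion.** The point stands as a mismatch between a hypothesis about means and a primary test that the data may turn into a rank test. It concerns the only primary endpoint and should be corrected.

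Its size is conditional. Under an assumed Shapiro-Wilk rule at 5%, rejection at equal means is about 9% when one arm has skewness 1. Power drops from 74% to about 57% in the 15%-by-12-points scenario, but by only about 2 points in the milder one. These figures rest on the assumed selection rule and the assumed shapes, none of which the article gives. The mismatch itself rests on the article's wording alone.

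The switch also buys little. At 143 per arm the t test held 4.8–5.8% at equal means in these skewed scenarios, so moderate non-normality is not a reason to leave the mean.

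**What to change.** Replace the choice of test with one mean-based primary analysis of EF change from baseline to 6 months, by MRI, used at both the interim and final looks whatever the distribution. A t test with unequal variances is enough. ANCOVA on the baseline EF already collected is an acceptable alternative, but the point does not require it. Report the mean difference in EF points with its confidence interval. Keep Mann-Whitney as a labelled sensitivity analysis that cannot replace the primary result. The stopping limits can stay as they are.

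The cost is a sentence or two of wording, with no new data and no change in patient numbers. The one downside is a slight loss of power if EF change turns out to be very heavy-tailed.
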